## 4. Methods

This is a randomized interventional clinical trial in healthy subjects organized at five sites of Mensura EDPB.

#### Inclusion criteria

- Employed by Mensura EDBP (should be an employee at least until the end of the study)
- Aged 18-55 years

#### Exclusion criteria

- Previously vaccinated against COVID-19
- Pregnant/breastfeeding women

#### Discontinuation criteria

All participants retain the right to end their participation in the study at any point in time. Participants who fail to provide the necessary information through the questionnaires, will be discontinued from the study, since any correlation analysis with biological measurements becomes impossible.

The primary objective of the study is to prove non-inferiority of anti-RBD binding antibody titers four weeks after the second dose of the 20µg versus 30µg study arm. If the primary outcome of the study reveals an inferiority of the 20µg dose, participants in the 20µg dose arm will be offered a third, 30µg dose of the study vaccine.

Although no correlate of protective immunity has been validated yet, a relationship between vaccine-induced SARS-CoV-2 antibodies and protection has been proposed (7).

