### 3.1. PRIMARY OBJECTIVE AND OUTCOME

- The primary objective is to prove non-inferiority of immunogenicity of a reduced BNT162b2 vaccine dose (20µg) versus the reference vaccine dose (30µg).
- The primary outcome is the geometric mean titer (GMT) of binding (IgG) antibodies specific to the receptor binding domain (RBD) of SARS-CoV-2 at four weeks after the second dose.

Data from the literature and from our own PICOV-VAC data indicate strong correlation between titers of RBD binding antibodies and neutralizing antibodies. As methods to measure RBD binding antibodies can be implemented more rapidly than neutralizing antibody assays, we consider that RBD binding antibodies are a good surrogate for neutralizing antibodies and can therefore be used as a primary endpoint for this study.

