### **Baseline activities**

After the participant has given written informed consent, the research nurse completes the Subject ID log with participant's name, national number and study number. The participant national number is collected and kept on site by the research nurse in the Subject ID log. Each of the participating sites will transfer this local Subject ID log at study closure to the TTP for data linkage, following the procedure detailed in the authorization of the Information Security Committee.

The research nurse creates a new participant in the study eCRF (hosted on LimeSurvey) and enters the date of consent, gender, year of birth, height, weight. They will also register whether the participant has had a past SARS-CoV-2 infection (i.e. positive nasopharyngeal swab, positive serology test).

Once the information is entered by the research nurse in the eCRF, the participant automatically receives an email (subject "Clinical Trial Message" and starting with "Dear Madam, Dear Sir") with a link to the data entry screens for the patient-reported-outcomes (PROMs). In order to have a second identity check, the participant first enters year of birth and their study number.

The research nurse can view the PROMs of his/her subjects and only exceptionally make corrections upon explicit request by the participant. Each such change will be logged and needs a justification. At all times the research nurse can indicate in the system the early end of study (and stop sending emails to the participant to complete the PROMs), e.g. in case of withdrawal of consent, if known to the research nurse. In case of withdrawal of consent, data already collected will be kept in the study data.

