### **Sampling visits**

An overview of the different sample types and volumes at each study visit is summarized in table 1. Venous blood will be collected on the day of the first and second dose as well as four weeks after the second dose, and six months and one year after the first dose. Five mL of blood will be collected from all study participants at all study visits. From a random selection of 20 participants per study arm (40 in total), 36mL of heparinized blood will be collected on the day of the first dose as well as four weeks after the second dose and six months after the first dose.

The sampling activity (date, sample types collected) is documented in the eCRF. Samples are handled as detailed in the sampling manual.

One week after each vaccination dose, participants will be invited by email and text message by the research nurse to fill in a questionnaire collecting information on the reactogenicity of the vaccine.

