### Data flow and management

Blood collection tubes as well as labelling stickers will be provided by Sciensano. For the entirety of the study, material will be provided in batch and a transport will be organized between Sciensano and the research sites. After collection, samples will be handled following the appropriate SOP.

Epidemiological and laboratory data will be linked via a unique code assigned to each participant. This code will start with the first letters of the research site location followed by a three digit number (e.g. "BRU\_001" for the first participant, "BRU\_002" for the second one, and so forth).

A sticker labelled with this code will be affixed by the research nurse on each tube at the time of sampling, and the same corresponding code will be entered in each questionnaire, enabling the link for data analysis. For the planned days, the labels will also include an identifier of this point (e.g. "D00", "D28" etc). This unique code must stay the same during all the duration of follow-up and a list of all participants and their assigned codes will be kept in a secure and protected way by the occupational physician.

Questionnaires are filled in online through LimeSurvey. Before sampling takes place, an email will be sent to the participant containing a questionnaire link and the unique participant code. It will take around

five minutes for the participant to fill in the questionnaire. If the questionnaire is not filled in yet at the moment of sampling, it will be filled in together with the research nurse. A confirmation email will be sent to the research nurse when a questionnaire is correctly received. LimeSurvey is a web application running on a server located within Sciensano's datacenter. The application and its associated database are located on the same server. It means there are no data located outside Sciensano. Access to the administration of the LimeSurvey application is restricted to a limited number of people involved in the administrative management of the survey, who are authenticated with a username and password. All files will be kept on the Sciensano SQL server with restricted access.

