### Statistical analyses

The analysis described here will be coordinated by the Sponsor. Any later analyses on the linked data will also be conducted by the Sponsor.

All of the participants who meet the eligibility criteria will be included in the main analysis. Descriptive analyses will be used to report participant characteristics. The level of antibody titers in each of the study arms will be analyzed with the Kruskal-Wallis test, while participant demographics (e.g. age, gender) will be taken into account (confounders). Furthermore, risk factors and correlations with antibody detectability will be evaluated. P-values below 0.05 will be considered statistically significant.

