### 7.2. BENEFITS

In general, the study will provide insight in the possibility of reducing the vaccine dosage required to achieve acceptable immune responses. This might help alleviate the current vaccine scarcity and speed up vaccination campaigns.

In particular, study participants will have the possibility to be vaccinated significantly earlier than foreseen by the Belgian national vaccination campaign, since they all belong to low priority groups. Secondly, those participants receiving a lower dose of the vaccine are expected to experience fewer and less severe side effects than they would with a full dose vaccination (5,9). Finally, if immune responses in the lower dose arm turn out to be inferior to the regular dose arm, these participants will be offered a third, regular dose to boost their immunity.

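### Discontinuing participants for missing questionnaires can prevent collection of the primary and later antibody samples, which need no questionnaire

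*Protocol*

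**What the plan says.** Protocol section 4, Discontinuation criteria: "Participants who fail to provide the necessary information through the questionnaires, will be discontinued from the study". The reason follows directly: "since any correlation analysis with biological measurements becomes impossible". The text does not say how much missing information triggers the rule, or what happens to samples and results already in hand.

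Five other places bear on it:

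- Statistical analyses: "All of the participants who meet the eligibility criteria will be included in the main analysis". No exclusion for missing questionnaires is stated.
- Baseline activities: "In case of withdrawal of consent, data already collected will be kept in the study data". This is said of consent withdrawal only, not of discontinuation by the study team.
- Data flow and management: "If the questionnaire is not filled in yet at the moment of sampling, it will be filled in together with the research nurse".
- Sampling visits: "One week after each vaccination dose, participants will be invited by email and text message by the research nurse to fill in a questionnaire". These forms record reactogenicity. Table 1 lists further questionnaires on the day of dose 1, at 6 months and at 1 year, and none on the day of dose 2 or four weeks after it.
- Section 7.2: "those participants receiving a lower dose of the vaccine are expected to experience fewer and less severe side effects".

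The primary outcome (section 3.1) is the anti-RBD IgG geometric mean titre four weeks after dose 2. The secondary outcomes (section 3.2) include further binding titres, neutralising titres and cellular responses, all measured in blood, together with safety and reactogenicity.

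**The concern.** The rule removes randomised, vaccinated people from follow-up for a reason that the primary comparison does not share. A correlation analysis that lacks a questionnaire can simply omit that participant, whereas a between-arm titre comparison that lacks a blood sample has lost an endpoint. Discontinuing non-responders does not recover the missing reactogenicity data either.

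Two things are at stake. The first is avoidable missing data in the primary titre and in the 6-month and 1-year titres. The second is possible imbalance. If response to a reactogenicity form depends on how the participant felt after the dose, and the protocol expects that to differ between 20µg and 30µg, then loss after randomisation can differ by arm. In a non-inferiority comparison such loss can shift the estimate in either direction.

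**Working it through.** **Timing.** Take dose 1 as day 0. The doses are three weeks apart (Vaccination), so dose 2 is on day 21 and the primary sample is on day 21 + 28 = 49. The one-week forms fall on about day 7 and day 21 + 7 = 28. Both precede the primary sample, so a participant discontinued over either form may never give it. The 6-month and 1-year forms come after the primary sample and cannot affect it. Discontinuation over the 6-month form puts the 1-year sample at risk.

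**Does nurse-assisted completion close the gap?** It applies at the moment of sampling. The Table 1 questionnaires coincide with sampling visits and are covered. The one-week forms are sent by email and text message between visits, and Table 1 shows no questionnaire at the next two sampling visits (dose 2 and four weeks later). Whether an overdue one-week form would be completed there is not stated, and Discontinuation criteria does not refer to the provision.

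**The plan's own figure.** Sample size gives 50 infection-naïve participants per group for 90% power, with margin 0.15 log10, SD 0.27, true difference 0 and a two-sided 2.5% error rate. The formula is n = 2(z_α + z_β)² × (SD/margin)², with (0.27/0.15)² = 3.24:

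- one-sided 1.25% (the literal reading): 2 × (2.241 + 1.282)² × 3.24 = 80.4, so 81 per arm
- one-sided 2.5%: 2 × (1.960 + 1.282)² × 3.24 = 68.1, so 69 per arm

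The figure of 50 does not reproduce. That is a separate matter and is no evidence for this point. It only fixes where the power figures below start.

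**Illustrative power cost.** The protocol gives no non-response rate, so the loss is assumed. Across all participants, 5% to 15% of 75 per arm is 3.75 to 11.25, about 4 to 11 people. The naïve group is 75 − 25 = 50 per arm if the ceiling of 25 previously infected per arm is reached (section 3). By normal approximation, power = Φ(0.15/(0.27 × √(2/n)) − z_α). At one-sided 2.5%:

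- n = 50: Φ(2.778 − 1.960) = 79.3%
- n = 45: Φ(2.635 − 1.960) = 75.0%

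The noncentral t distribution gives slightly lower values (n rounded down):

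| Assumed loss | n per arm | Power, one-sided 2.5% | Power, one-sided 1.25% |
|---|---|---|---|
| 0% | 50 | 78.5% | 69.2% |
| 5% | 47 | 76.0% | 66.1% |
| 10% | 45 | 74.1% | 63.9% |
| 15% | 42 | 71.1% | 60.5% |
| 20% | 40 | 68.9% | 58.0% |

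A 10% loss costs 78.5 − 74.1 = 4.4 points or 69.2 − 63.9 = 5.3 points. If all 75 per arm counted, with the same SD, a 10% loss (n = 67) would take power from 92.2% to 89.1% at one-sided 2.5%, a cost of 3.1 points.

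**Illustrative bias.** If a fraction f of an arm is lost and the lost differ from the remaining by s log10, that arm's mean shifts by f × s. With 10% lost from one arm only and s = 0.2, the shift is 0.02, which is 0.02/0.15 = 13% of the margin. With 10% against 5% lost and s = 0.1 in both arms, the shift is (0.10 − 0.05) × 0.1 = 0.005, or 3% of the margin. All of these inputs are assumed, and the direction is unknown.

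**The case against.** The strongest defence is that the rule will rarely be applied. Nurses complete overdue forms at sampling visits, and section 5.2 provides for text-message reminders, so the rule would reach mainly people who refuse even with help. If that help extends to the one-week forms, a missing form after dose 2 would be completed at the visit where the primary sample is drawn. This stands as a limit on frequency. It is not a full answer, because coverage of those forms is not stated and the rule is not made conditional on it.

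Questionnaires also matter. They supply reactogenicity, which is a secondary objective and the stated reason for enrolling more than the minimum. That stands too, but it justifies pursuing the forms, not giving up the blood samples of those who do not return them.

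Four stronger readings are tempting and should not be drawn.

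- **Valid antibody results are thrown away.** The rule does not say so, and Statistical analyses points the other way. The handling of results from discontinued participants may also be set out in a statistical analysis plan that is not at hand.
- **The rule flatly contradicts the main analysis population.** Ending follow-up and defining who is analysed are different things, and both sentences can hold for someone whose titre is already known. The tension arises only for someone discontinued before the primary sample, who is to be included but has no endpoint.
- **Safety observation ends.** Monitoring of adverse reactions runs for the study period through a separate form completed by the study nurse. Nothing says that it stops for a discontinued participant, so this is an inference.
- **The rule explains power below 90%.** The starting power of 78.5% or 69.2% comes from the sample size calculation, and the rule accounts only for any further fall.

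**Conclusion.** The point holds in a limited form. The protocol states a rule that is broader than its own reason requires, and following it can leave the four-week primary sample and the 6-month and 1-year samples uncollected in randomised participants. Loss related to arm is plausible given the expected dose difference in side effects, but it is not shown, and participants are blinded to their dose.

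The size cannot be determined from the protocol. The cost of about 4 to 5 points of power rests on an assumed 10% loss, on the ceiling for infected participants being reached, and on the primary comparison being made in the naïve group. The bias range of 3% to 13% of the margin rests on assumed loss fractions and titre gaps. The reason to change the rule is that the loss is avoidable and serves no stated outcome, not that it is known to be large.

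**What to change.** Replace the sentence in Discontinuation criteria with a rule to this effect: participants with missing questionnaires stay in the study for all scheduled blood samples and adverse-reaction monitoring, remain in the primary analysis, and are omitted only from analyses that need the missing form.

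Reconcile the section with three others:

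- Data flow and management: say whether completion with the nurse covers the one-week reactogenicity forms, and at which visit.
- Baseline activities: say that data already collected are kept after any early end of participation, not only after withdrawal of consent.
- Statistical analyses: confirm that a missing questionnaire does not affect inclusion in the main analysis.

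The first one-week form falls between the two doses, and the protocol does not say what discontinuation at that point means for the vaccination schedule. The sponsor should reconcile Discontinuation criteria with Vaccination on this.

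The cost is a short protocol amendment under section 7.7, with sponsor approval and ethics committee approval as applicable. It adds no visits or samples beyond those already scheduled.

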## Sample size

The primary analysis is a non-inferiority comparison at 28 days after the second dose, for the GMT of antibodies binding to the RBD of SARS-CoV-2, comparing the reference dose (30µg BNT162b2) with the reduced dose (20µg BNT162b2).

Currently available data from published and ongoing COVID-19 vaccination trials indicate that:

- RBD-specific antibody titers (GMT, arbitrary units) 28 days after the second dose of BNT162b2 equals 2125. The standard deviation on the log scale (base 10) is 0.27 (PICOV-VAC trial).

The following assumptions are made in the sample size calculations:

- The non-inferiority margin is -0.15 absolute difference of GMT on log scale (base 10), between a reduced dose and regular dose vaccine schedule.
- The standard deviation of GMT on the log10 scale is 0.27 for BNT162b2, based on the currently available data.
- The true difference of GMT on log10 scale is 0.
- A two-sided 2.5% family-wise error rate (at cohort level).

Based on these assumptions, the comparison between both doses will need a minimum of 50 participants (infection naïve) per group to achieve 90% power. In order to be able to better evaluate reactogenicity however, we aim for a larger sample size.

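### The level for the primary non-inferiority test is not consistently stated: two-sided 2.5% under Sample size, p below 0.05 under Statistical analyses

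*Protocol*

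**What the plan says.** Protocol section 3.1 names one primary outcome: "The primary outcome is the geometric mean titer (GMT) of binding (IgG) antibodies specific to the receptor binding domain (RBD) of SARS-CoV-2", measured four weeks after the second dose. Section 3 gives two equally randomized arms. Under Sample size, "The primary analysis is a non-inferiority comparison at 28 days after the second dose", so there is one primary test. The same section lists the design inputs:

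- Margin: "The non-inferiority margin is -0.15 absolute difference of GMT on log scale (base 10")
- Spread: an SD of 0.27 in log10 units, taken from existing data on the vaccine
- Assumed true effect: no difference between the doses
- Error rate: "A two-sided 2.5% family-wise error rate (at cohort level")

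From these it derives a minimum of 50 infection-naïve participants per group for 90% power.

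The Statistical analyses section states who enters the main analysis and then says: "The level of antibody titers in each of the study arms will be analyzed with the Kruskal-Wallis test". It goes on to risk factors and correlations, and ends with "P-values below 0.05 will be considered statistically significant". It gives no sidedness, no separate level for the primary comparison, and no reference back to the 2.5%.

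**The concern.** Two levels are given, and the protocol does not say which one governs the primary verdict. A two-sided 2.5% level corresponds to a 97.5% interval, and a conventional two-sided 5% level to a 95% interval. The non-inferiority bound is looser under the second, so the same data could pass under one and fail under the other. An analyst could adopt either level and point to a section of the protocol in support.

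The phrase about a family-wise rate at cohort level adds to the uncertainty. With one outcome and one comparison there is no family of primary tests, and the phrase is not explained. A reader cannot tell whether 2.5% is the level of the single test or an amount still to be divided.

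The verdict is used during the trial. The Blinding/unblinding section plans an analysis at 28 days after the second dose, and a finding of non-inferiority there means that unblinding is not needed before the end of the trial.

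**Working it through.** **Inputs** (Sample size, and section 3 for the arms): margin -0.15 log10; SD 0.27 log10; true difference 0; 1:1 allocation; 50 infection-naïve per group as the stated minimum; 150 in total, hence 75 per arm, of whom up to 25 may be previously infected.

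**Step 1. Does the stated sample size reveal the intended level?** For one-sided level a and 90% power, n per group = 2 × [0.27 × (z(1-a) + 1.2816) / 0.15]².

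- Two-sided 2.5% (tail 1.25%, z = 2.2414): 80.4, so 81.
- One-sided 2.5% (z = 1.9600): 68.1, so 69.

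Neither gives 50. One-sided 5%, which the protocol does not state, gives 55.5, so 56. The stated 50 is close to what one-sided 2.5% needs for 80% power: 2 × [1.8 × (1.9600 + 0.8416)]² = 50.9, so 51. The sample size therefore does not settle which level was meant.

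**Step 2. Lowest observed result that passes.** Non-inferiority is met when the observed log10 difference exceeds -0.15 + t × SE, with SE = 0.27 × √(2/n) and t on 2n - 2 degrees of freedom. The GMT ratio is 10 to that power.

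| n per arm | SE | Interval | t | Lowest difference | Lowest GMT ratio |
|---|---|---|---|---|---|
| 50 | 0.0540 | 97.5% | 2.276 | -0.027 | 0.940 |
| 50 | 0.0540 | 95% | 1.984 | -0.043 | 0.906 |
| 75 | 0.0441 | 97.5% | 2.264 | -0.050 | 0.891 |
| 75 | 0.0441 | 95% | 1.976 | -0.063 | 0.865 |

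At 50 per arm, for example, an observed ratio of 0.92 passes with the 95% interval and fails with the 97.5% interval. The rows for 75 apply SD 0.27 to arms that may include previously infected participants. That is an assumption, because the protocol's calculation counts infection-naïve participants.

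**Step 3. How often would the choice matter?** With a true difference of 0, the chance of passing is Φ(0.15/SE - z).

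- 50 per arm: 0.15/0.0540 = 2.778. At tail 1.25%, Φ(0.536) = 70.4%. At tail 2.5%, Φ(0.818) = 79.3%. The gap is 8.9 points.
- 75 per arm: 0.15/0.0441 = 3.402. At tail 1.25%, Φ(1.161) = 87.7%. At tail 2.5%, Φ(1.442) = 92.5%. The gap is 4.8 points.

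The noncentral t gives 69.2% and 78.5% at 50 per arm, and 87.1% and 92.2% at 75. The gaps of 9.3 and 5.1 points lead to the same conclusion.

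**The case against.** The strongest reply is that the two statements do not collide. The 2.5% is attached to the non-inferiority comparison, while p below 0.05 follows a Kruskal-Wallis test of difference and a sentence on risk factors. On that reading 0.05 is the general level for the other tests. This is possible, and it is why the point is an inconsistency in statement rather than a proven contradiction. It does not remove the point: the same paragraph covers the main analysis and the arm comparison of titers, and it exempts nothing.

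A second reply is that one-sided 2.5% was meant, which equals two-sided 5% and would reconcile the sections. That is plausible, but the text says two-sided, so Sample size would then need correcting.

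A third is that with a single comparison a family-wise rate is simply the level of the test. That is right. The word is redundant and changes no threshold. Section 2 does call the 150 subjects a cohort, so the phrase may mean the whole study, but this is not explained.

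Three stronger readings are tempting and are not supported:

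- A reader might take p below 0.05 as one-sided and infer a 90% interval and an error rate of up to 5%. No section states a one-sided 5% test.
- A reader might infer that this level by itself decides the third-dose offer. Discontinuation criteria and Blinding/unblinding tie that offer to a finding of inferiority, and failing to show non-inferiority is not the same as showing inferiority.
- A reader might count the missing 90% power as a result of the conflict. The figure of 50 falls short under each level tried, so it is a separate defect that this correction must also deal with.

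**Conclusion.** The point holds as an inconsistency in the stated level for the primary verdict, between a 97.5% and a 95% interval. The one-sided error rate at the margin is 1.25% or 2.5%. The passing GMT ratio moves from about 0.94 to 0.91 at 50 per arm, and from 0.89 to 0.87 at 75. The verdict would differ in roughly 9% or 5% of trials.

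These sizes rest on SD 0.27, a true difference of 0, a t-based comparison of log10 means, no dropout (the protocol gives no rate), and reading p below 0.05 as two-sided. The figures at 75 also need SD 0.27 to hold with previously infected participants included. The effect is modest, but it concerns the trial's main conclusion and should be settled before the data are seen.

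**What to change.** 1. State one level and its sidedness for the primary test, in the same terms under Sample size and Statistical analyses. For example: non-inferiority is met if the lower limit of the two-sided 95% confidence interval (one-sided 2.5%) for the log10 GMT difference, 20 µg minus 30 µg, exceeds -0.15. If two-sided 2.5% is kept, the interval must be 97.5% in both places.
2. Delete the family-wise and cohort-level wording, or define it.
3. Limit p below 0.05 to the analyses other than the primary one.
4. Restate power at 50 per group for the chosen level: about 79% at one-sided 2.5%, or about 70% at two-sided 2.5%. If 90% is to be kept, restate the minimum instead, as 69 or 81 infection-naïve participants per group.
5. Reconcile the non-inferiority verdict with the inferiority wording under Discontinuation criteria and Blinding/unblinding, so that it is clear how a result showing neither is classified. What follows clinically is for the sponsor to decide.

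Items 1 to 3 cost a few sentences, and item 4 a short recalculation. Stating the level and the true power alters no treatment, visit or sample. Keeping 90% power could affect recruitment: 75 per arm with 25 previously infected leaves 75 - 25 = 50 infection-naïve, below either minimum.

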## 3. Objectives and outcomes

We aim to include 150 adults aged 18-55 years from five Mensura EDPB sites. These will be equally randomized in two study arms receiving two doses of:

- Arm 1: 20µg BNT162b2
- Arm 2: 30µg BNT162b2

We aim to include up to 25 previously SARS-CoV-2 infected subjects per arm. The objectives of this study include assessing the immunogenicity (both humoral and cellular), safety and reactogenicity of a reduced vaccine dose.

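### The stated minimum of 50 infection-naïve participants per group gives about 70% or 79% power under the protocol's own inputs, not 90%

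*Protocol*

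**What the plan says.** The Sample size section (under 4. Methods) describes the comparison and lists every input needed to check it:

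- Design: "The primary analysis is a non-inferiority comparison at 28 days after the second dose".
- Margin: "The non-inferiority margin is -0.15 absolute difference of GMT on log scale (base 10").
- Standard deviation: "The standard deviation of GMT on the log10 scale is 0.27 for BNT162b2".
- Assumed effect: "The true difference of GMT on log10 scale is 0".
- Error rate: "A two-sided 2.5% family-wise error rate (at cohort level").

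From these it concludes that "the comparison between both doses will need a minimum of 50 participants (infection naïve) per group to achieve 90% power". It gives no allowance for dropout. It explains the larger planned enrolment by the wish to assess reactogenicity better, not by power.

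Section 3 (Objectives and outcomes) plans 150 adults in two equal arms and adds: "We aim to include up to 25 previously SARS-CoV-2 infected subjects per arm". Trial randomization allocates without regard to infection history and stratifies only on age and gender.

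**The concern.** The inputs and the result stand in the same section, and the result is presented as following from the inputs. It does not, so no later analysis plan could make the section correct.

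The figure matters because the infection-naïve comparison may end up at exactly this minimum: 75 − 25 = 50 per arm. At that number, a 20 µg dose that is truly equal on the primary outcome would fail to show non-inferiority in about 21% to 31% of trials, against the 10% that the protocol implies. Anyone who weighs the trial's chance of answering its primary question is relying on the 90%.

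**Working it through.** **Inputs** (Sample size section, with equal arms from section 3): margin d = 0.15, SD = 0.27, true difference 0, 1:1 allocation, power 90% (z = 1.282). The error rate is read in three ways:

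- two-sided 2.5% as written, which puts 1.25% in the non-inferiority tail (z = 2.241);
- one-sided 2.5%, the likeliest alternative meaning (z = 1.960);
- one-sided 5%, which this section does not state and which is included only as a lenient bound (z = 1.645).

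**Step 1. Try to reproduce 50 per group.**

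n per group = 2 × (z_alpha + z_beta)² × (SD/d)², with (0.27/0.15)² = 3.24, so n = 6.48 × (z_alpha + z_beta)².

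- Two-sided 2.5%: 6.48 × (2.241 + 1.282)² = 80.4, so 81 (82 with the t distribution).
- One-sided 2.5%: 6.48 × (1.960 + 1.282)² = 68.1, so 69 (t: 70).
- One-sided 5%: 6.48 × (1.645 + 1.282)² = 55.5, so 56 (t: 57).

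None of these gives 50.

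**Step 2. Power at 50 per group.**

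Standard error = 0.27 × √(2/50) = 0.054, and 0.15/0.054 = 2.778. Power = Φ(2.778 − z_alpha).

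| Error rate | Power (normal) | Power (t) |
|---|---|---|
| Two-sided 2.5% | Φ(0.537) = 70.4% | 69.2% |
| One-sided 2.5% | Φ(0.818) = 79.3% | 78.5% |
| One-sided 5% | Φ(1.133) = 87.1% | 86.7% |

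**Step 3. Power if all 75 per arm are analysed.** This assumes that an SD of 0.27 also holds when previously infected participants are included, which the protocol does not show.

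Standard error = 0.27 × √(2/75) = 0.0441, and 0.15/0.0441 = 3.402.

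- One-sided 2.5%: Φ(3.402 − 1.960) = about 92% (t: 92.2%).
- Two-sided 2.5%: Φ(3.402 − 2.241) = about 88% (t: 87.1%).

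**Step 4. Effect of loss.** With an assumed 10% loss from 50, that is 45 naïve per arm, the standard error is 0.27 × √(2/45) = 0.0569 and 0.15/0.0569 = 2.635. Power is about 75% (one-sided 2.5%) or 65% (two-sided 2.5%), and about one point lower with the t distribution.

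**Step 5. What would produce about 50?**

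- 80% power at one-sided 2.5%: 6.48 × (1.960 + 0.842)² = 50.9, so 51.
- 90% power at one-sided 2.5% with a margin of about 0.175, close to log10(1.5) = 0.176.
- 90% power at one-sided 2.5% with an SD of about 0.231.
- 90% power at two-sided 2.5% with a margin of about 0.190 or an SD of about 0.213.

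So more than one misstated input could explain the figure.

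**The case against.** The best defence is that 50 is only a floor. The protocol enrols 75 per arm, section 3 sets 25 previously infected as an upper limit, and the Statistical analyses section puts all eligible participants into the main analysis. On that reading the primary comparison could have 75 per arm and, at one-sided 2.5%, about 92% power. This stands as a limit on the point. A reader might infer that the trial's actual power is 69–79%. The protocol does not support that, because the range applies to 50 naïve participants per arm and the naïve number may be higher. The defence does not rescue the stated minimum, however. It needs an SD assumption that the protocol does not support for a mixed group, and at the error rate as written it still gives only 87–88%.

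Three further readings are tempting and go too far:

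- That 50 must come from a 1.5-fold margin. Step 5 shows that 80% power fits about as well, and a smaller SD fits too. The protocol does not say which input is misstated.
- That admitting fewer previously infected participants would restore 90%. With 5 per arm (70 naïve), power is about 85% at two-sided 2.5%. It reaches 90% only at one-sided 2.5% and with no dropout. At the error rate as written, 90% is out of reach within 150 participants, since 2 × 81 = 162.
- That the low power would turn an inconclusive result into a finding of inferiority. How the Discontinuation criteria and Blinding/unblinding sections treat a failed non-inferiority test is a separate question, and it adds nothing to this one.

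**Conclusion.** The point holds for the stated minimum. Under the section's own margin, SD and true difference, 50 infection-naïve participants per group give about 70% power at the error rate as written and about 79% at one-sided 2.5%. That is a shortfall of roughly 11 to 21 percentage points against the claimed 90%. The required number is 81 per group, or 69 if one-sided 2.5% was meant. The choice between normal and t calculations moves these figures by about one participant or one percentage point, so rounding does not explain the gap.

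The result rests on a two-sample comparison of mean log10 titres with equal arms and no loss. The power the trial will have depends on how many naïve participants are enrolled and on who enters the primary comparison.

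**What to change.** In the Sample size section:

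1. Settle the error rate for the non-inferiority test and say whether it is one-sided or two-sided.
2. Go back to the original calculation and reconcile sample size, power, margin and SD, correcting whichever was misstated. Do not change the margin after data are seen.
3. State the number per group that follows. With the present inputs this is 81 (t: 82) at two-sided 2.5%, or 69 (t: 70) at one-sided 2.5%.
4. State the power at the planned numbers: about 70% or 79% for 50 naïve per arm, and about 87–88% or 92% for 75 per arm, with the SD assumption for the latter made explicit.

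The cost is a rewritten section and a less favourable stated power. This correction adds no participants. Keeping 90% power at two-sided 2.5% with the present margin and SD would need more than the planned 150, so the sponsor should either accept and report the lower power or decide openly on a different design.
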